## **8 SAFETY MANAGEMENT**

### **8.1 Clinical Adverse Events**

Clinical adverse events (AEs) will be monitored throughout the study.

### **8.2 Adverse Event Reporting**

Since the study procedures are not greater than minimal risk, SAEs are not expected. If any unanticipated problems related to the research involving risks to subjects or others happen during the course of this study (including SAEs) they will be reported to the NJIT IRB in Unanticipated Problems Involving Risks to Subjects. AEs that do not meet prompt reporting requirements will be summarized in narrative or other format and submitted to the IRB at the time of continuing review (if continuing reviews are required), or will be tracked and documented internally by the study team but not submitted to the IRB (if continuing reviews are not required).

---

## 9 STUDY ADMINISTRATION

### 9.1 Treatment Assignment Methods

#### 9.1.1 Randomization

A member of the study team will randomize case subjects who consent to participate into one of the treatment groups at the conclusion of their initial assessment. Participants will be randomly allocated by a member of the study team using a pre-determined block randomization procedure. Subjects will be randomized in a 1:1 ratio. Block sizes will be multiples of 4, to reduce the potential size of imbalance across the 2 intervention arms. All participants will be assigned a unique identification number at enrollment, which the study team will use to track subjects' date of enrollment, assigned treatment group, and timeline of their treatment phase.

#### 9.1.2 Blinding

Physicians specializing in concussion will identify subjects and then refer them to trained members of the study team who will handle the consent and randomization processes. Physicians will continue routine clinical care for all subjects. Licensed, practicing optometrists will complete the vision assessments, with a different optometrist completing outcome visit 1 and outcome visit 2 for each participant in order to remain blinded.

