#### **3.1.2 Study Treatment Phase**

Case subjects who enroll in the study will be randomized into two groups, one completing SCC+OBVAT and the other completing only SCC in phase 1. A member of the study team will assign subjects to one of the two arms using a pre-determined block randomization procedure. After randomization to a treatment arm, subjects will be provided with instructions on study procedures based on their treatment arm. Subjects in the SCC+OBVAT group (arm 1) will be contacted by a trained and certified vision therapist to schedule and complete their OBVAT sessions. The vision therapist will conduct all OBVAT sessions with participants and will instruct them on the in-home reinforcement. Subjects in both arms will

---

continue to follow-up with the physician treating their concussion as applicable. After the first 6 weeks and completion of outcome visit 1, subjects in the SCC only group (arm 2) will be contacted by a trained vision therapist to schedule and complete their OBVAT sessions.

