### **3.2 Allocation to Treatment Groups and Blinding**

A member of the study team will randomize case subjects who consent to participate into one of the treatment groups at the conclusion of their initial assessment using a random number generator. Optometrists will be blinded to the treatment group.

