#### **3.4.3 Index/Case Subject Exclusion Criteria**

- 1) Previous office or home-based vision therapy, orthoptics, home-based near-target push-ups, or pencil push-ups.
  - 2) Amblyopia or constant strabismus or strabismus surgery.
  - 3) High refractive error: Myopia  $\geq 6.0\text{D}$  sphere; Hyperopia  $\geq 5.0\text{D}$  sphere; Astigmatism  $\geq 4.0\text{D}$ ; Anisometropia  $> 1.5\text{D}$  difference between eyes; prior refractive surgery.
  - 4) Manifest or latent nystagmus evident clinically.
  - 5) Systemic diseases that affect accommodation, vergence or ocular motility (i.e. multiple sclerosis, Graves' thyroid disease, myasthenia gravis, diabetes, chemotherapy, or Parkinson's disease).
  - 6) Vertical heterophoria greater than  $1\Delta$ .
  - 7) Parents/guardians or subjects who, in the opinion of the Investigator, may be non-compliant with study schedules or procedures.
  - 8) Non-English speakers.
  - 9) For participants within the NJIT clinical site the additional exclusion criteria is necessary for fMRI imaging:
-

- A. Non-removable metal in the body.
- B. Subjects who are pregnant, planning on becoming pregnant during the study duration, or breastfeeding.
- C. Subjects who are metal workers.

Subjects that do not meet all of the enrollment criteria may not be enrolled. Any violations of these criteria must be reported in accordance with IRB Policies and Procedures.

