### **5.1.3 Other Evaluations, Measures**

- **Clinical Examination:** A standard optometric clinical exam that includes near point of convergence, positive fusional vergence, dissociated phoria, corrected visual acuity, unilateral cover test, stereopsis, monocular amplitude of accommodation, accommodative facility, vergence facility at near and far, negative fusion vergence, and eye movement and vestibular evaluation will be performed by a practicing, licensed optometrist.
  - **Patient-Reported Outcome Surveys:**
-

- CISS-Con
  - Vision Quality of Life with Time Survey (VisQual-T)
  - **VET:** An ISCAN eye tracker integrated into an Oculus head mounted display DK2 will track and record subjects' eye movement. The VET is about a 20 minute protocol comparing vergence steps at the beginning and end of a test while performing vergence steps and ramps, and saccades.
  - **VRS3:** An ISCAN eye tracker integrated into an Oculus head mounted display DK2 will track and record subjects' eye movement. The VRS3 is about a 15 minute protocol of vergence ramps, vergence steps, and saccades objective eye movements.
  - **Intervention:** This study involves a therapeutic intervention testing the effect of OBVAT in adolescent and young adults with PPCS-CI. Subjects will be randomly assigned to either an SCC+OBVAT or SCC only group using a pre-determined block randomization procedure.
    - **SCC+OBVAT:** subjects assigned to the SCC+OBVAT arm will attend bi-weekly OBVAT sessions with a trained and certified vision therapist. OBVAT has four phases. The first phase will be designed to manage some of the visual/vestibular issues common in PPCS-CI using eye movements associated with head and body movement. In phase 2, techniques will be used to stimulate gross convergence, positive fusional vergence and monocular accommodative therapy using Brock string, Vectograms, Computer Orthoptics and Lens Accommodative Rock, respectively. Once the subject can perform these tasks with ease, s/he will graduate to the third phase which is ramp fusional vergence and monocular accommodative therapy with Vectograms, Aperture Rule, Lifesaver Cards and Lens Accommodative Rock. The final stage will consist of jump fusional vergence and binocular accommodative facility. The initial phase is used to remediate vestibular issues if present but if there are no vestibular issues, then this phase will be omitted.

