## **7 STUDY INTERVENTION**

### **7.1 Description**

This study involves a therapeutic intervention testing the effect of OBVAT in adolescents and young adults with a PPCS-CI. Subjects will be randomly assigned to either SCC+OBVAT or SCC only arm using a random number generator. Subjects in the SCC+OBVAT arm will be asked to complete 12 one-hour biweekly OBVAT sessions in Phase 1 and an additional 4 one-hour biweekly OBVAT sessions in Phase 2. Subjects in the SCC only arm will be asked to follow SCC as instructed by their clinician for 6 weeks. Subjects will also be asked to complete at-home reinforcement during their OBVAT intervention.

All subjects will complete an optometric clinical exam, a self-reported symptom survey, fMRI and a suite of vision assessments at their study visits.

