### **9.6 Informed Consent/Assent and HIPAA Authorization**

A member of the study team and/or the PI will obtain consent and assent, if applicable, from all eligible subjects that agree to participate in the research. Eligible subjects will be consented in one of two ways: using a paper consent form or electronically via REDCap. For all eligible subjects, the consent form will outline the procedures of the study and indicate the risks and benefits of participation. Subjects will be informed that their participation in the study is voluntary and will not impact the quality of care they receive for their concussion. In addition, they will be given sufficient time to ask questions and consider participation. All subjects will have the option to receive a copy of the consent form, which includes a description of the research and contact information for the study team. Subjects that turn 18 during the course of the study will be re-consented. To ensure that consent and assent are documented in the same location, assent will also be documented as part of the same electronic form if electronic consent is being obtained. The electronic

---

consent form will include a checkbox for consent by subjects who are at least 18 years of age or a parent/legal guardian of subjects under 18. A separate checkbox for assent will be included for subjects between the ages of 11 and 17.

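### Allocation could be foreseen or re-drawn: the unblinded study team both consents and randomizes, by two unreconciled methods and with no concealment step

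*Protocol*

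**What the plan says.** **Who does what.** Section 9.1.2 has physicians identify subjects and "refer them to trained members of the study team who will handle the consent and randomization processes". Section 9.6 adds: "A member of the study team and/or the PI will obtain consent and assent, if applicable, from all eligible subjects". Section 9.5 has the study team screen against the eligibility criteria, and section 9.1.1 has it track each subject's assigned group.

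**Which method.** Three sections describe a block procedure:
- 3.1.2: "A member of the study team will assign subjects to one of the two arms using a pre-determined block randomization procedure"
- 5.1.3: "Subjects will be randomly assigned to either an SCC+OBVAT or SCC only group using a pre-determined block randomization procedure"
- 9.1.1: subjects are "randomly allocated by a member of the study team using a pre-determined block randomization procedure"; the ratio is 1:1 and block sizes are multiples of 4.

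Two sections describe something else:
- 3.2: a team member randomizes "at the conclusion of their initial assessment using a random number generator"
- 7.1: subjects are "randomly assigned to either SCC+OBVAT or SCC only arm using a random number generator"

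**Blinding and access.** Sections 3.2, 9.1.2 and 9.1.3 blind the optometrists and nobody else. Arm 1 starts OBVAT at once, while arm 2 has 6 weeks of SCC first (section 4.2). Section 9.2 restricts each site to its own data in REDCap.

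**What is absent.** No section names an independent holder of the sequence, a central or web release, sealed envelopes, or a lock on eligibility before the arm is revealed.

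**The concern.** Concealment of the next assignment is what stops recruiters from letting the expected arm influence who enters and when. Blinding the examining optometrists protects outcome measurement but does nothing for entry.

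Here the team that screens and consents also allocates, knows past assignments, and works from a protocol that prints the ratio and the block multiple. The two descriptions of the method fail in different ways. A block sequence can be inferred from its earlier part, or read if it is accessible. A generator run by the same person at the end of the visit can be run again.

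There is also a discretionary gate before entry: the exclusion in section 3.4.3 of families or subjects who "in the opinion of the Investigator, may be non-compliant with study schedules or procedures". The arms differ sharply in immediate burden: arm 1 has 12 office sessions before Outcome Visit 1 and arm 2 has none. Someone who foresees the arm thus has both a reason and a means to include, exclude or delay a family.

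What is at stake is the comparison of OBVAT+SCC with SCC alone at Outcome Visit 1, the only randomized contrast of therapy against no therapy. The intention-to-treat approach in section 6.3.2 does not correct selection that happens before randomization.

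**Working it through.** The protocol states no figure on this point, so there is none to reproduce. The calculation shows how predictable the block version could be.

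**Inputs.** From section 9.1.1: 1:1 allocation and block sizes in multiples of 4. From the abstract: about 150 case subjects. From section 3.3.2: site targets of 30–50, 30–50 and 50–75. Assumed: staff know the block size and all earlier assignments in the current block, and guess whichever arm has more places left (a coin toss when level).

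**Block of 4, by position**
- First: nothing is known, so P(correct) = 1/2.
- Second: three places remain, two in the other arm, so P(correct) = 2/3.
- Third: with probability 1/3 the first two were the same arm and the third is certain; otherwise it is a coin toss. P(correct) = 1/3 × 1 + 2/3 × 1/2 = 2/3.
- Fourth: always certain, P(correct) = 1.

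Correct guesses: (1/2 + 2/3 + 2/3 + 1)/4 = 2.833/4 = 70.8%.
Certain in advance: (0 + 0 + 1/3 + 1)/4 = 33.3%.

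Exact enumeration of larger blocks gives:

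| Block size | Certain in advance | Guessed correctly | Of 150: certain / correct |
|---|---|---|---|
| 4 | 33.3% | 70.8% | 50 / 106 |
| 8 | 20.0% | 66.6% | 30 / 100 |
| 12 | 14.3% | 64.3% | 21 / 96 |
| Simple draws, not repeated | 0% | 50% | 0 / 75 |

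With a random mix of blocks of 4 and 8, and a guess made only from the running imbalance, about 68% are still guessed correctly (simulation).

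**One sequence shared by three sites.** Sites were weighted by the midpoints of their targets (40, 40 and 62.5), N = 150, and staff saw only their own site's assignments. Guessing against the site's own imbalance is right about 52% of the time. Guessing the opposite of the site's last assignment is right about 57% (blocks of 4) or 55% (blocks of 8). These are simple rules, not a proven optimum.

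**From predictability to bias.** Suppose staff shift the average prognosis of entrants by +d when they expect one arm and by −d when they expect the other. With p the proportion guessed correctly, the expected difference between arms is

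bias = 2 × d × (2p − 1).

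For blocks of 4 and d = 0.25 SD: 2 × 0.25 × (2 × 0.708 − 1) = 0.21 SD. The protocol gives no value for d, so a range is needed:

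| d (assumed) | Blocks of 4, p = 0.708 | Blocks of 8, p = 0.666 | Shared sequence, p = 0.52 to 0.57 | Simple draws, p = 0.50 |
|---|---|---|---|---|
| 0.10 SD | 0.08 SD | 0.07 SD | 0.01 to 0.03 SD | 0 |
| 0.25 SD | 0.21 SD | 0.17 SD | 0.02 to 0.07 SD | 0 |
| 0.50 SD | 0.42 SD | 0.33 SD | 0.04 to 0.14 SD | 0 |

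The last column assumes that no draw is repeated. The protocol offers no basis for putting a number on repeated draws.

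**The case against.** The strongest reply is that the protocol is silent here rather than wrong. It speaks of a procedure. It does not say that recruiting staff hold or see a sequence, that the block size is fixed, or that each site has its own sequence. Block sizes appear in the plural, which allows them to vary. It refers to team members collectively and does not say that one individual both consents and allocates a given subject. Allocation follows consent and the initial assessment, so steering would need the arm to be foreseen before consent. The compliance exclusion is the investigator's judgement, and physicians make the first identification. Both arms eventually receive 16 sessions, which weakens the motive. Finally, a block sequence is normally made with a random number generator, so the two descriptions could refer to one process.

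Most of this limits the size of the problem, and it stands. A reader might infer that allocation in this trial is foreseeable as a matter of fact, or that staff know every assignment because they hold the list. The documents support neither. Foreseeability arises only under the block version and depends on what staff can see; under simple draws it does not arise. Nor do the two descriptions strictly contradict each other.

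The reply does not supply the missing safeguard. Section 3.2 reads most naturally as a draw made at the visit, so a site could follow either version, and neither is protected. Own-site data access helps only if one sequence spans the sites, which is not stated. It may not help at NJIT, which is both a clinical site and the Data Coordinating Center (section 3.3.2). Section 9.1 is where treatment assignment is fixed, so this is not a detail that a protocol would normally leave to the SAP.

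**Conclusion.** The point holds in conditional form. As written, the unblinded team that screens and consents also allocates; the method is described in two unreconciled ways; the block structure is disclosed; and nothing conceals the next assignment. Allocation could be foreseen or re-drawn. The documents do not show that it will be.

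The upper bound on predictability is 33% certain and 71% guessable with blocks of 4 (20% and 67% with blocks of 8). It requires a known block size and sight of every earlier assignment in the block. With one sequence across three sites and own-site data only, simple guessing rules succeed about 52% to 57% of the time, and with simple, unrepeated draws 50%.

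Any bias also depends on an assumed prognostic shift. At 0.25 SD it runs from zero, through 0.02 to 0.07 SD for a shared sequence, up to about 0.21 SD for blocks of 4. The upper figure is a worst case and should not be read as an estimate for this trial. The change is still worth making, because it is cheap and protects the trial's only randomized comparison.

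**What to change.** State one allocation method, in the same words, in sections 3.1.2, 3.2, 5.1.3, 7.1 and 9.1.1:

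- Someone at the Data Coordinating Center with no part in recruitment prepares the block sequence with randomly varying block sizes. The separation must be explicit because NJIT also recruits. A random number generator may be used to create the sequence, and the text should then say that this is its only role.
- State whether there is one sequence or one per site.
- Remove the block sizes from the text that sites hold, and keep them in a restricted document.
- Release each assignment through a central system only after consent, eligibility (including the compliance judgement) and the initial assessment have been entered and locked. REDCap is already used for data capture, with an audit trail (section 9.2), and could serve if its set-up supports this; the protocol does not mention a randomization function.
- State in section 9.1.2 that staff who screen and consent have no access to the sequence and cannot repeat a draw.

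The cost is system set-up, wording changes in the sections named, and the need to enter eligibility data before a subject can be allocated. Varying the block sizes reduces predictability only modestly (about 68% guessable with a mix of 4 and 8, if all earlier assignments are seen), so the central release and the restricted access matter more.

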#### 9.1.3 Unblinding

The optometrists completing the optometric examinations will be unblinded at the completion of the entire study.

### 9.2 Data Collection and Management

1. **Confidentiality.** Data will be managed and stored using the research-focused electronic data capture system REDCap, under an agreement with the software's development consortium, led by Vanderbilt University. REDCap supports two secure, web-based applications designed exclusively to support data capture for research studies. REDCap is a PHP web application served by Apache Tomcat over a 128-bit SSL connection using a signed certificate. The application relies on a study-specific data dictionary defined in an iterative self-documenting process that will be conducted by all members of the research team. The data dictionary is the foundation for custom case report form design and validated coding of variables. Authentication of research staff will be performed via LDAP using CHOP's enterprise Active Directory service. The application generates a complete audit trail of user activity, provides reporting, and has an automated export mechanism to common statistical packages (SAS, SPSS, Stata, R/S-Plus). Subjects at each site will be assigned a unique ID code and only the local study team at each individual site will be able to view the link between the unique ID and direct patient identifiers, with the exception of a designated study team member at CHOP who will be able to review all consent documents for quality assurance purposes. A separate master list will be maintained as a password-protected file on a secure drive at each site and will contain the subject ID number, name, MRN, date of birth and dates of service.
-

During testing, data may be collected on coded paper forms that include a limited data set, including relevant dates (i.e. date of birth, date of injury, and dates of testing) as well as email and phone number. After the completion of testing, these data will be transferred into the REDCap and the paper forms will either be stored securely in a locked research office or scanned onto the secure research server at each site and destroyed. In addition, each of the objective assessments results in an electronic test report from the specific device utilized. Results from these tests will be stored on the secure storage network at each site and may be input by the study team into the same REDCap database utilized for standard clinical data.

In order to keep protected health information (PHI) from disclosure, all data collected as part of eye movement recordings or MRI (NJIT clinical site only) will be coded and identified only by a code label assigned to the participant upon entry into the study. When a need for further medical evaluation or treatment is identified during the research, participants will be appropriately referred and upon obtaining consent, the information made available to the health-care provider.

2. **Security.** The REDCap MySQL database is replicated in real time to a completely redundant instance of MySQL. The redundant instance is available for restoration of the primary database or for manual failover in the case of primary database failure. Time-stamped backup files are made from the replicated database daily by CHOP Research Information Systems using automated backup routines. Backup files are encrypted and transferred to a secure file server accessible only to designated personnel. A rolling seven-day window of backup files is maintained in an immediately available online state, with a larger window maintained in a compressed file archive available at a reduced speed of access. Daily destructive database backup files are stored on the database server and are deleted only after successful backup of the entire database to file. In the event of data error, loss or corruption, Research personnel will work with CHOP Research Information Systems to determine the most appropriate recovery strategy. Data and backups are stored in the CHOP Research Information Systems Storage Area Network (SAN). Access to the SAN directories where data are stored will be limited to Research Information Systems personnel, with authentication performed using CHOP's enterprise Active Directory service. Access to the REDCap database will be limited to members involved in the study, and each site will only have access to their own site level data. The master sheet linking PHI with the unique subject ID will be maintained securely at each site so only members of the study team can access.

The data from the objective eye movement recordings will be stored locally on the computer hard drive that is encrypted and password protected. Data will be automatically saved to an external hard drive that is also encrypted, and password

---

protected, and automatically saves unidentifiable data to the HIPPA compliant ShareFile or OneDrive.

All MRI images will be coded and stored on a password protected Rutgers research servers and/or password protected PCs. MRI images will be shared with NJIT via secure sharing system ShareFile.

The data collected on paper forms during testing will be secured in a locked research office.

3. **Anonymization, de-identification or destruction.** All PHI collected from this study will be retained until the study is completed, including full data acquisition, analysis, and publication. PHI will only be retained after completion of the study if subjects have indicated a willingness to be contacted for future studies or to future use of their data. We will maintain a separate master sheet with PHI for subjects who agree to future contact or future use of their data. Coded data will be maintained separately and will only be linked to PHI through the subject ID. Subjects who do not consent to future contact or the future use of their data will have their data retained for the longer of either (A) 6 years after completion of the study or (B) 2 years after the last marketing approval or if no application is filed or approved, 2 years after the FDA is notified of discontinued application. Once the FDA record retention requirements have been met, subjects who do not consent to future use of their data or future contact will have their data destroyed.

